### Clinical and laboratory monitoring

Eligible subjects will undergo a confirmatory test for influenza A or B at the screening visit on Day 1. To be included in the primary analysis population, influenza virus infection will be confirmed by reverse transcription-polymerase chain reaction (RT-PCR). A full description of the visit and assessment schedule is provided in Table 2. The following outcome measures will be assessed by subjects or their parent/guardian and recorded in an ePRO diary from postdose Day 1 to postdose Day 9: influenza symptom severity and body temperature (axillary) using an electronic thermometer taken right before or at least 4 h after administration of acetaminohen, if relevant; the severity of seven influenza symptoms (cough, sore throat, headache, nasal discharge/nasal congestion, feverish or chills, muscle ache or joint pain, and fatigue) will be assessed by subjects ≥ 7 years who are deemed able to assess influenza symptoms themselves; the severity of two influenza symptoms (cough, nasal discharge/nasal congestion) will be assessed by a parent/guardian for subjects < 7 years and/or those ≥ 7 years who are considered by the investigators to not able to assess influenza symptoms themselves.

**Table 2 Tab2:** Visit and assessment schedule

Day	1		2 +1 day	3	4	5 -1 to +2 days	6	7	8	9	10 −1 to +4 days 4	Discontinuation +14 days
Visit	1^a^		2			3						
	Pre dose	Post dose										
Informed consent	X											
Inclusion/exclusion criteria	X											
Demographics, clinical characteristics, and medical history	X											
Enrollment and randomization	X											
Baloxavir administration		X										
Oseltamivir administration		X	X	X	X	X						
Diary (ePRO)												
Body temperature	X	X^a^	qid		bid							
Influenza symptom severity	X	X^a^	bid									
Medical examination^b^	X		X			X					X	X
Vital signs	X		X			X					X	X
Influenza RIDT	X^c^											
SARS-CoV-2 test	X^d^		X^e^									
Influenza virus tests (RT-PCR, titer, RNA, PA, or NA sequence)	X		X			X					X	X
Influenza virus serum antibody titer test (HI method)	X											
Intrahousehold influenza infection rate questionnaire											X	X
TEAE reporting	X	X	X	X	X	X	X	X	X	X	X	X

X denotes assessment to be undertaken

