*bid* twice a day; *COVID-19* coronavirus disease 2019; *ePRO* electronic patient-reported outcome; *HI* hemagglutination inhibition; *NA* neuraminidase; *PA* polymerase acidic protein; *qid* four times a day; *RIDT* rapid influenza diagnostic test; *RT-PCR* reverse transcription-polymerase chain reaction; *SARS-CoV-2* severe acute respiratory syndrome coronavirus 2; *TEAE* treatment-emergent adverse event

^a^Not measured if study drug taken after 18:00

^b^Participants’ height and body weight are measured on Day 1 (predose/screening)

^c^Participants who have an RIDT and/or other influenza virus test within 48 h of symptom onset but before written informed consent do not need to take an RIDT and/or other influenza virus test on Day 1

^d^Participants who are determined to be SARS-CoV-2 negative according to the COVID-19 clinical guideline in Japan (https://www.mhlw.go.jp/content/000712473.pdf) before giving written consent do not need to undergo a SARS-CoV-2 test on Day 1

^e^This test will be conducted according to the COVID-19 clinical guideline as appropriate

The presence of SARS-CoV-2 infection will be assessed using an approved rapid SARS-CoV-2 test which includes but not limited to SARS-CoV-2 antigen test. For influenza virology tests, nasopharyngeal swabs will be tested for influenza virus type/subtype, viral RNA load and infectious influenza virus titer, and amino-acid substitutions in the PA protein subunit and neuraminidase (NA) using Sanger sequencing and a nested PCR (LSI Medience Corporation, Tokyo, Japan), as previously described [27]. Medical examinations will be conducted by investigators, and vital signs will be measured by investigators, nurses, or medical technicians, as appropriate.

For the intrahousehold (cohabitants or family members who live together) influenza virus transmission rate, household members who give their written consent will be provided with a paper questionnaire on Day 1 (predose). Completed questionnaires will be collected on Day 10. The questionnaire covers information on the following: household size (including age category); the number of household members infected from the pediatric subject’s enrollment up to Day 10 or until discontinuation from the study; and the date of each household member’s diagnosis of influenza infection, use of anti-influenza drug therapies, and the date of their recovery of normal body temperature (< 37 °C).

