Virological endpoints Infectious influenza virus titer and the amount of virus RNA (determined by RT-PCR) at each time point Change from baseline in infectious influenza virus titer and amount of virus RNA (determined by RT-PCR) at each time point Proportion of participants whose influenza virus titer and quantitative RT-PCR are above and below the lower limits of quantification at each time point Time to the first cessation of viral shedding based on the influenza virus titer, defined as the time postdose until virus titers reach the lower limit of quantification for the first time Time to sustained cessation of viral shedding based on influenza virus titer, defined as the time from the last positive virus titer postdose to the first virus titer that is below the lower limit of quantification	
Exploratory endpoints	
Emergence of amino-acid substitutions (PA/I38X and NA/H275Y) in subjects who are RT-PCR positive for influenza infection pre- and postdose. Treatment-emergent influenza virus substitutions in PA/I38 or NA/H275 will be defined as amino-acid substitution occurring between Day 1 and the last time point where the influenza virus RT-PCR cycle threshold is < 31 for the H1 subtype or < 29 for the H3 subtype Rate of intrahousehold influenza infection	
Safety	
AEs, AEs possibly related to baloxavir or oseltamivir, SAEs, vital signs	

*AE* adverse event; *NA* neuraminidase; *PA* polymerase acidic protein; *RT-PCR* reverse transcription-polymerase chain reaction; *SAE* serious adverse event

The main secondary endpoints include the time to sustained resolution of influenza symptoms (cough, nasal discharge/nasal congestion, and body temperature) for at least 72 h; the time to resolution of fever (normal body temperature < 37.5 °C) for at least 12 h; the time to sustained resolution of fever for at least 72 h; the proportion of subjects with resolution of fever at each time point; the time to resolution of seven influenza symptoms (cough, sore throat, headache, nasal discharge/nasal congestion, feverish or chills, muscle ache or joint pain, and fatigue) for at least 21.5 h; the incidence of influenza-related complications and those influenza-related complications seen particularly in children (influenza-associated encephalitis or encephalopathy, febrile seizures, myositis); the use of antibiotics for treatment of infectious disease secondary to influenza infection; and the change from baseline in infectious influenza virus titer.

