The present study will be one of the first to assess treatment-emergent amino-acid substitutions for both PA and NA among children treated with baloxavir and oseltamivir in the same study. Several studies suggest that treatment-emergent antiviral resistance is more likely to emerge in children than in adults [27, 28, 31, 32], which is of concern because of the potential risk of transmission of virus variants to close contacts [33]. The frequency of treatment-emergent PA/I38X amino-acid substitutions that are associated with reduced susceptibility to baloxavir has been shown to be more than twofold higher in children than in adults [27, 28]. Findings from a global 7-year surveillance study showed that treatment-emergent resistance to oseltamivir (NA/H275Y for N1 viruses and NA/R292K for N2 viruses) is highest among young children (1–5 years) compared with adults and older children or adolescents [31, 32]. Although it has not been established why young children may be more susceptible to the emergence of antiviral treatment resistance, it is thought that influenza virus variants emerge in response to selective pressure during drug treatment, possibly as a result of the immature immune response in children, at a time when drug concentrations in plasma have started to wane [27, 28, 32].

Findings from the two open-label noncomparative studies of weight-adjusted baloxavir suggest that baloxavir is likely to be clinically effective compared with NAIs in Japanese children aged 6 to < 12 years [27, 28]. In both studies, there was a rapid reduction in virus titer, and the median TTIA was 45 h. Gastrointestinal events were the most commonly reported AEs in both studies, which is consistent with the findings in non-Japanese children in miniSTONE-2 [24] and with the findings from a large postmarketing surveillance study of baloxavir in Japan that included 896 children aged < 12 years [29]. In this surveillance study, adverse drug reactions occurred more frequently in children than in adults, but diarrhea was the most common adverse reaction in all age groups. Although these real-world studies provide valuable information on the use of baloxavir in Japan, no clinical studies have been conducted to confirm the effectiveness of baloxavir against a comparator in children (6 to < 12 years) with influenza infection in Japan.

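### The exploratory substitution endpoint counts NA/H275Y but not NA/R292K, which the article itself names as the N2 marker, so oseltamivir-associated substitutions are under-counted in H3N2 infections

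*Protocol article*

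**What the plan says.** Protocol article, Outcome measures and endpoints, Table 3 (exploratory endpoints): the endpoint is "Emergence of amino-acid substitutions (PA/I38X and NA/H275Y) in subjects who are RT-PCR positive for influenza infection pre- and postdose". The operational rule repeats the restriction to two positions: "Treatment-emergent influenza virus substitutions in PA/I38 or NA/H275 will be defined as amino-acid substitution occurring between Day 1" and the last time point at which the "RT-PCR cycle threshold is < 31 for the H1 subtype or < 29 for the H3 subtype". No other neuraminidase position is listed.

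Protocol article, Discussion: in describing a global surveillance study, the article assigns the oseltamivir markers by neuraminidase type, "treatment-emergent resistance to oseltamivir (NA/H275Y for N1 viruses and NA/R292K for N2 viruses". It also describes this trial as "one of the first to assess treatment-emergent amino-acid substitutions for both PA and NA among children treated with baloxavir and oseltamivir" in one study.

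Protocol article, Clinical and laboratory monitoring: swabs are tested for type and subtype, and the laboratory looks for "amino-acid substitutions in the PA protein subunit and neuraminidase (NA) using Sanger sequencing" together with a nested PCR. This is worded generally and is not limited to one codon. Type B is not excluded from the trial: "Eligible subjects will undergo a confirmatory test for influenza A or B at the screening visit on Day 1".

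**The concern.** The endpoint uses one marker for each drug, but the two markers do not cover the same viruses. PA/I38X can be counted in any H1 or H3 infection that meets the cycle-threshold rule. The only NA marker counted is the one the article links to N1. The N2 marker that the article names is left out of both the endpoint and the treatment-emergent definition, although the H3 cut-off shows that H3 infections are in scope.

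What is at stake is the meaning of the oseltamivir figure. A low NA count could reflect little emergence, or it could reflect a season with many H3N2 infections, and the endpoint as defined cannot tell the two apart. The error has one direction: it can lower the count of oseltamivir-associated substitutions and leaves the baloxavir count alone. The Statistical analysis section says that qualitative data are summarised with the difference between groups in proportions and its 95% CI. If this endpoint is handled that way, the undercount passes into the difference.

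**Working it through.** The article states no emergence rate and no subtype mix, so there is no planned figure to reproduce. The check is a reading of the definitions, followed by an illustration under assumed values.

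**Step 1: what is countable, by infection.** I take H1 viruses to carry N1 and H3 viruses to carry N2 (assumption: the article gives cut-offs by H and markers by N).

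| Infection | Cut-off in Table 3 | PA/I38X counted | NA marker named in the Discussion | That NA marker counted |
|---|---|---|---|---|
| H1N1 | Ct < 31 | yes | H275Y | yes |
| H3N2 | Ct < 29 | yes | R292K | no |
| Type B | none given | not specified | none given | not specified |

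The H3N2 row holds the contradiction. It lies within the article and needs no outside source.

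**Step 2: size under equal emergence.** Let s be the N2 share of evaluable influenza A infections on oseltamivir, and r the true emergence rate, assumed equal for H275Y in N1 and R292K in N2.

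Counted rate = r × (1 − s).

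With the 66 planned oseltamivir children (Statistical analysis section), all assumed to have influenza A and to be evaluable, and r = 5%, the true expected number is 66 × 0.05 = 3.3. Counted cases are 66 × (1 − s) × 0.05:

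| N2 share s | Counted cases | Counted rate |
|---|---|---|
| 0 | 3.3 | 5.0% |
| 0.25 | 2.48 | 3.75% |
| 0.50 | 1.65 | 2.5% |
| 0.75 | 0.83 | 1.25% |
| 1 | 0 | 0% |

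At s = 0.50, true rates of 2%, 5% and 10% read as 1.0%, 2.5% and 5.0%. If R292K were counted for N2, the full 3.3 cases at r = 5% would be recovered at every s.

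**Step 3: unequal emergence.** With rate r1 for H275Y in N1 and r2 for R292K in N2, the share of events missed is s·r2 / [(1 − s)·r1 + s·r2]. At s = 0.50:
- r2 half of r1: 0.25 / (0.5 + 0.25) = 33% missed
- r2 equal to r1: 0.5 / (0.5 + 0.5) = 50% missed
- r2 twice r1: 1 / (0.5 + 1) = 67% missed

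**Step 4: chance that at least one case goes uncounted.** With 33 H3N2 children on oseltamivir (half of 66), P = 1 − (1 − r)^33, which is 49%, 82% and 97% at r = 2%, 5% and 10%. The endpoint needs positive RT-PCR before and after dosing, so fewer will be evaluable. With about half, taken as 16, P = 1 − (1 − r)^16:
- r = 2%: 1 − 0.724 = 28%
- r = 5%: 1 − 0.440 = 56%
- r = 10%: 1 − 0.185 = 81%

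**The case against.** The strongest reply is that the endpoint is worded as the emergence of two named substitutions and is not called an oseltamivir resistance rate. It is exploratory, no statistical tests are planned, and NA is sequenced in general terms, so R292K could probably be read from the data later. All of this limits the consequence and stands. It does not remove the mismatch: the table fixes which positions count, and a marker reported only after the results are seen is weaker than one named beforehand.

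A second reply is that the size rests wholly on assumed rates and an assumed subtype mix. That is correct. In addition, the surveillance finding in the Discussion places the highest oseltamivir resistance at ages 1–5, below this trial's age range. The direction of the error does not depend on these assumptions; the amount does.

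Three stronger readings are tempting, and the article does not support them.
- A reader might infer that oseltamivir resistance in H3N2 is zero by construction. The exact statement is that R292K is never counted. A change at NA position 275 in an H3N2 virus would still qualify.
- A reader might infer that type B infections can never contribute an event. The article gives no type B cut-off, which leaves their status unspecified; the full protocol may settle it. The gap applies to both groups and has nothing to do with the H3N2 problem.
- A reader might infer that a headline comparison between drugs is tilted against baloxavir. The Discussion speaks of assessing PA and NA substitutions and promises no comparison. The main novelty it claims is the randomised active-controlled design in Japanese children.

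**Conclusion.** The point holds in a limited form. Table 3 leaves out the N2 marker that the article's own Discussion names, while bringing H3 infections into scope through a cycle-threshold cut-off. Followed as written, the endpoint understates oseltamivir-associated substitutions whenever R292K emerges in an H3N2 child, and has no matching loss for PA/I38X.

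The amount cannot be fixed from the article. With equal emergence by subtype, the share missed equals the N2 share: a quarter at 25%, half at 50%, all at 100%. With H3N2 in half of infections, and R292K emerging from half as often to twice as often as H275Y, the share missed runs from 33% to 67%. These are illustrations, not estimates.

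The effect is confined to an exploratory, descriptive endpoint. The primary and secondary endpoints are not affected. It is worth correcting because the correction is nearly free. The missing type B cut-off is a separate and minor matter of clarity.

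**What to change.** 1. In Table 3, define the NA marker by subtype, with H275Y for N1 and R292K for N2, in both the endpoint and the definition of treatment-emergent substitution.
2. Report PA and NA substitutions by subtype, using the evaluable children of that subtype as the denominator, so that the season's mix does not drive the pooled figure.
3. As a minor clarification, state whether type B is inside this endpoint. If it is, give its cut-off and markers; if not, keep type B children out of the denominator.

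The cost is wording and a table row. Swabs are already subtyped and NA is already sequenced from the same samples, so on the article's general description of the sequencing no new visit or sample is needed. The laboratory should confirm that the sequenced region covers position 292.

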**Fig. 1 Fig1:**
[figure not shown]
Trial timeline

Screen failures are defined as pediatric patients who do not meet the eligibility criteria. Reasons for discontinuation from the trial will include the following: decision to discontinue by a pediatric subject or their parent/legal guardian; death or any serious adverse event (SAE) or intolerance to study drug as determined by the investigator; a positive severe acute respiratory syndrome coronavirus 2 (SARS-CoV-2) test or suspected coronavirus disease 2019 (COVID-19); any repeated deviation from the protocol (e.g. repeated use of concomitant prohibited drugs) for the duration of the trial; or any other reason as determined by the investigator.

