The assessment of the safety and tolerability of study drugs will include the frequency and nature of adverse events (AEs), AEs related to study drugs, SAEs, and vital signs. All AEs will be managed in accordance with good medical practice by the participating physicians as appropriate. An AE will be considered “serious” if it results in death, is life-threatening, requires hospitalization or prolongation of hospitalization, or is persistent or results in significant incapacity or substantial disruption to daily life. All deaths and immediately life-threatening events, whether related or unrelated to study drug, will be reported to the CRB as soon as possible. All SAEs will be shared with all investigators participating in the study. If there is a reasonable possibility that the study procedure causes an unanticipated SAE, the sponsor of the study will report the SAE to the Pharmaceuticals and Medical Devices Agency in Japan.

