The number of participants with AEs, SAEs, AEs leading to discontinuation, and AEs possibly related to study drug, as well as the number of deaths, will be summarized for each treatment group, and AEs will be coded using the Medical Dictionary for Regulatory Activities. Incidence rates will be calculated as the proportion of participants in the analysis population, and 95% CI using the Clopper-Pearson method. The change in each vital sign from baseline (predose) will be calculated for each treatment group.

Data obtained outside the allowable ranges described in Table 2 will be treated as missing, and values will not be imputed at each visit. All analyses will be conducted using SAS® software, version 9.4 (SAS Institute Inc., Cary, NC, USA).

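### As worded, the seriousness definition makes persistence alone a criterion for a serious adverse event; the sentence needs a small correction

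*Protocol article*

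**What the plan says.** The definition is in the protocol article, Outcome measures and endpoints, in the safety paragraph after Table 3. It opens: "An AE will be considered “serious” if it results in death, is life-threatening, requires hospitalization or prolongation of hospitalization". From the hospitalization limb to its close it reads: "requires hospitalization or prolongation of hospitalization, or is persistent or results in significant incapacity or substantial disruption to daily life". The limbs are alternatives, so meeting any one makes the event serious.

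The term is then used in three places:

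- **Statistical analysis.** The per-group safety summaries include "The number of participants with AEs, SAEs, AEs leading to discontinuation, and AEs possibly related to study drug". The next sentence gives the estimator: "Incidence rates will be calculated as the proportion of participants in the analysis population, and 95% CI using the Clopper-Pearson method". SAEs are also listed under Safety in Table 3.
- **Outcome measures and endpoints.** "All SAEs will be shared with all investigators participating in the study".
- **Trial design, in the text after Fig. 1.** The reasons for discontinuing from the trial include "death or any serious adverse event (SAE) or intolerance to study drug as determined by the investigator".

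**The concern.** Seriousness is meant to separate events by their consequences. Here one limb separates them by duration. Taken at its word, mild diarrhea that begins on Day 2 and is still present at the Day 10 visit is serious, with no incapacity and no admission, while the same diarrhea resolved on Day 3 is not. The example is realistic: the Discussion reports gastrointestinal events as the most common adverse events in the two earlier Japanese pediatric studies.

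What is at stake is the meaning of a reported safety result. If the sentence is applied literally, the SAE count per arm mixes grave events with minor ones that merely lasted. If some of the roughly 82 sites apply it literally and others do not, the count also depends on who read it. The word has no stated duration and treatment is open-label, so nothing in the article fixes how the limb is to be applied.

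**Working it through.** **1. Grammar of the rule.** Taking the limbs in order, with the adverse event as the subject of each:

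| Limb | What it turns on |
|---|---|
| results in death | grave outcome |
| is life-threatening | grave outcome |
| requires or prolongs hospitalization | grave outcome |
| is persistent | duration only |
| results in significant incapacity | grave outcome |
| results in substantial disruption of daily life | grave outcome |

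Incapacity is the object of a second verb, 'results in', which comes after the word 'persistent'. It therefore cannot limit that word. The fourth limb is complete in itself and is the only one with no element of gravity.

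**2. Search for a correction elsewhere.** The Methods text, Tables 1 to 3 and the abbreviation list contain no definition of persistence by duration or severity and no second version of the seriousness rule.

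**3. Weight of one event.** The article states no expected SAE rate, so there is no figure to reproduce. The planned arm sizes are 134 and 66 (Statistical analysis). The safety population is those who receive at least one dose, so the actual denominators may differ slightly.

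- Baloxavir: 1/134 = 0.75 percentage points.
- Oseltamivir: 1/66 = 1.5 percentage points.

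**4. What added events do to the reported interval.** The Clopper-Pearson limits for x events in n children are the 2.5% quantile of Beta(x, n − x + 1) and the 97.5% quantile of Beta(x + 1, n − x). For x = 0 the lower limit is 0 and the upper limit is 1 − 0.025^(1/n).

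| Children with an SAE | n = 134 | n = 66 |
|---|---|---|
| 0 | 0% (0 to 2.7) | 0% (0 to 5.4) |
| 1 | 0.7% (0.0 to 4.1) | 1.5% (0.0 to 8.2) |
| 3 | 2.2% (0.5 to 6.4) | 4.5% (0.9 to 12.7) |

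The counts of 0, 1 and 3 are illustrations, not forecasts. They show only that when the count is small, a few reclassified events visibly change what is reported.

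**5. Reach into efficacy.** The primary endpoint, time to illness alleviation, uses two respiratory symptoms and axillary temperature, not seriousness. The ePRO diary that records them runs to Day 9 (Clinical and laboratory monitoring), and restricted mean survival time is also taken to Day 9 (Statistical analysis). The Day 10 visit has a window of −1 to +4 days (Table 2), so it opens on the last diary day. Table 2 lists the same virus tests and household questionnaire under Day 10 and under Discontinuation.

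**The case against.** The strongest reply is that this is a drafting slip with an obvious intended meaning. All the other limbs concern gravity, so an experienced investigator would read persistence as describing the incapacity. The article also appeared in August 2021, whereas recruitment was to run from November 2020 to April 2021 under a protocol approved in October 2020. Sites would have classified events from that protocol and the eCRF, which are not shown and may be worded correctly. Safety reporting is descriptive, the definition is the same in both arms, and deaths, all adverse events and events leading to discontinuation are summarized separately.

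Most of this stands, and it limits the consequences. It does not remove the error: the published sentence is the stated rule, and following it gives a classification that its other limbs do not support.

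A reader might draw two stronger conclusions that the documents do not support:

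- **That SAE counts will be inflated, perhaps with non-grave events outnumbering grave ones.** This needs literal use by sites, a rate of mild adverse events, the share that persist, and a true SAE rate. The documents give none of these.
- **That a mild lingering event could cost a child's efficacy follow-up, because any SAE is a listed reason for discontinuation.** An event judged persistent at the Day 10 visit comes when the diary is ending or has ended. Discontinuation is also not clearly automatic, since the listed item closes with a reference to the investigator's determination. An earlier judgment of persistence is possible in principle, but nothing in the article shows that it would occur.

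**Conclusion.** The sentence is wrong as written. It makes persistence a sufficient criterion for seriousness and so, read literally, classes any lingering adverse event as an SAE.

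The size is known only per event: 0.75 points in the baloxavir arm and 1.5 points in the oseltamivir arm, at the planned numbers. The total effect is unknown because no adverse event durations are given. It could be nil if the full protocol and the eCRF carry the right wording, or if sites read the sentence as evidently intended. No effect on the primary endpoint or on efficacy follow-up is shown. This is a minor correction to a safety definition, not a flaw in the design or the analysis.

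**What to change.** Reword the last limb so that 'persistent' modifies the incapacity: it should begin *results in persistent or significant incapacity* and continue as it does now. Then confirm that the full protocol and the eCRF seriousness check use that wording, and tabulate SAEs on that definition. If either document carries the free-standing limb, review any event recorded as serious on persistence alone before the tables are produced. The discontinuation list relies on the same term, so check that it is read with the corrected definition; no change to the discontinuation rule is proposed here.

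The cost is one sentence in the protocol text and a matching line in the eCRF guidance. It needs no new data and no change to the design or the statistical methods.
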